### Process evaluation RCT

Alongside the RCT, a process evaluation will be conducted using the RE-AIM (Reach, Effectiveness, Adoption, Implementation, and Maintenance) framework [53], to examine the STEPS intervention regarding feasibility, experiences, satisfaction, barriers and facilitators for implementation. The RE-AIM framework has been adjusted to the design and target population of this study (see Table 3 for an overview), e.g., adding the dimension ‘tailoring’ to the framework. The measurements of the process evaluation will be based on data collected during the study and data collected by process evaluation questionnaires. To do so, cancer survivors in the intervention group will receive a short questionnaire, together with the six-month follow-up questionnaire (T1). Cancer survivors in the control group will be asked what care they have received during the study period. Participating occupational therapists and reintegration consultants will receive their own specified questionnaire at the end of the intervention period.

**Table 3 Tab3:** Overview of process measures according to the Re-Aim framework

Dimensions	Topics	Assessment method
Reach (individual level)	1. Patient response versus nonresponse rate. 2. Characteristics of participants compared to non-participants. 3. Percentage of patients who completed the intervention.	1. Response and non-response data. 2. Percentages excluded and reasons for exclusion (using drop-out and loss-to-follow-up data, reported reasons for declining participation, data from NCR on source population). 3. Process evaluation questionnaire (patient version).
Effectiveness (individual level)	4. Effect of the intervention on primary and secondary outcomes. 5. Unintended adverse effects of the program.	4. Data regarding primary and secondary outcome measures. 5. Self-reported in process evaluation questionnaire.
Tailoring (individual level)	6. Extent to which the content, intensity, and duration of the intervention was tailored to the patient’s needs, limitations, wishes and capacities. 7. Extent to which the intervention enabled the patient to return to work or continue work. 8. Extent to which the return-to-work/work retention plan fitted the work-related needs, capacities and wishes of the patient.	6–8. Process evaluation questionnaire (patient version).
Adoption (organizational level)	9. Attitude from the occupational therapists and reintegration consultants regarding the intervention after adoption of the program. 10. Extent to which the program corresponded with organizational goals and capacities of the participating centres hospital and the reintegration agency.	9. Process evaluation questionnaire (occupational therapist and reintegration consultant version). 10. Data regarding (cost-)effectiveness of the intervention and data from the process evaluation questionnaire (occupational therapist and reintegration consultant version).
Implementation (individual and organizational level)	11. The extent to which recruitment was conducted according to protocol. 12. The extent to which the intervention was delivered according to protocol. 13. Extent to which the intervention was delivered according to budget.	11. Evaluating through what recruitment path (via the NCR, health care practitioners or social media) 12. Process evaluation questionnaire (occupational therapist and reintegration consultant version). 13. Measured by evaluating study procedures.
Maintenance (individual, organizational level)	14. Extent to which the program produced long-term individual behaviour change and established return to work. 15. Extent to which organizations will sustain the program in the future. 16. Extent to which future patients are likely to participate in the program.	14. Data regarding the primary and secondary outcome measures. 15. Process evaluation questionnaire (occupational therapists and reintegration consultant version). 16. Process evaluation questionnaire (patient version).

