	Contract type (fixed/temporary)	X			A	X	X		A
	Shift work	X			A	X	X		A
	Company size and sector	X			A	X	X		A
	Time since first day of sick leave	X			A				–
	Employment status partner (if applicable)	X			A				–
	(duration of) Caregiving leave				–	X	X		A
Work	Social support from supervisor/colleagues	X			A	X	X		A
	Job insecurity	X			A	X	X		A
	Need for recovery	X			A^c^	X	X		A
	Work accommodation	X			A^c^	X	X		A
	Impact of COVID-19 on work	X			A^c^	X	X		A
	Work attitude	X			A	X	X		A
	Self-efficacy	X			A	X	X		A
	Work-family balance	X			A^c^	X	X		A
	Work intention	X			A	X	X		A
	Fear of COVID-19	X			A	X	X		A
	Expectations regarding return to work	X			A				–
Process measures			X		P				–
Economic evaluation	Quality of life	X	X	X	E				–
	Health care consumption	X	X	X	E				
	Productivity loss	X	X	X	E				

^a^*P* Primary outcome variable, *S* Secondary outcome variable, *A* Additional variable, *M* Modifier, *E* Economic evaluation variables, *P* Process variables

^b^Only completed by participants who were on sick leave at baseline

^c^Only completed by participants who (partly) returned to work

^d^The partner will be asked regarding the medical status of the cancer survivor

**Table 2 Tab2:** List of primary, secondary and additional variables and their assessment methods

		Instrument	# items	Rating scale	Operationalization
Work outcomes	Working hours per week	Asking participants for their current number of actual working hours	1	n/a	Continuous
	Change in working hours (%)	Asking participants for their current number of actual working hours and their contractual working hours at baseline.	1	n/a	Continuous (actual working hours at follow-up as a percentage of contractual working hours at baseline).
	Employment status	Asking participants whether they are at work or not at work	1	n/a	Dichotomous
	Time to return to work	Asking participants about their first day of returning to work, from which we will estimate the number of calendar days between the first day of sick leave and the first day of work, either fulltime or part-time, for at least 28 consecutive days without recurrence.	1	n/a	Continuous
	Sick leave	Asking participants about the number of days they have been on sick leave in the past 6 months	1	n/a	Continuous

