For all analyses, unadjusted models and models adjusted for relevant confounders will be presented. In addition to the main analysis described above, subgroup analyses will be performed (see Table 1 for a list of potential confounders and subgroups). No interim analyses will be conducted for this study, as due to the low risk of the intervention it is unlikely that results of such analyses would lead to termination of the study.

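### The only adverse-effect item described is one six-month self-report in the intervention arm, so explicit adverse effects have no control comparator and no 12-month round

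*Protocol article*

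**What the plan says.** Adverse effects are named in one place, Table 3 under Process evaluation RCT. Among the Effectiveness topics it lists "5. Unintended adverse effects of the program", and the matching assessment method is "Self-reported in process evaluation questionnaire".

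The text above the table says who gets which process questionnaire:

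- Survivors on STEPS: "cancer survivors in the intervention group will receive a short questionnaire, together with the six-month follow-up questionnaire (T1").
- Controls: "Cancer survivors in the control group will be asked what care they have received during the study period".
- Providers: "Participating occupational therapists and reintegration consultants will receive their own specified questionnaire at the end of the intervention period".

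Table 1 (Measurements) marks the row "Process measures" at T1 only. Under Statistical analyses, the RCT section justifies having no interim analysis on the ground that "due to the low risk of the intervention it is unlikely that results of such analyses would lead to termination of the study".

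Separately, Table 1 and the Economic evaluation section place working hours, employment status, sick leave, work ability, QLQ-C30, EQ-5D-5L, health care consumption and productivity loss in both arms at T0, T1 and T2.

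**The concern.** STEPS supports early return to work, from 3 months after diagnosis, and the invitation encourages people who do not yet feel ready to take part. Its plausible harms are a return that fails, conflict at work, or health made worse by working. All three also occur under usual care, so a count from one arm cannot be read as an effect of STEPS. The programme may last up to six months, so a single question at T1 can fall just as it ends, with half of the follow-up still to come.

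The primary outcome scores more hours as benefit. The Methodological considerations section itself allows that an increase may not be desirable for every survivor. A comparison of identifiable setbacks would balance that outcome, and the described collection does not provide one.

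**Working it through.** The point concerns who is asked what and when, so the main check sets the passages side by side.

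**Step 1. Explicit adverse-effect item, by arm and time**

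| | T1 (6 months) | T2 (12 months) |
|---|---|---|
| Intervention arm | yes (process questionnaire) | none described |
| Control arm | none described (care received only) | none described |

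One cell of four is filled. No between-arm contrast can be formed at either time.

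**Step 2. Both-arm measures that could show harm indirectly**

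- At T1 and T2: working hours, employment status, sick-leave days over the past 6 months, work ability, QLQ-C30 (including fatigue and pain scales), EQ-5D-5L and health care use. Work functioning is completed only by those who have at least partly returned.
- The primary and secondary outcomes are compared by GEE, with T1 and T2 effects reported separately. The T2 sick-leave question covers months 6 to 12.

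**Step 3. What these measures do not identify**

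- Sick leave is a six-month total. Alone, it does not separate relapse after a return from never having returned.
- Time to return to work is fixed by the first return lasting at least 28 consecutive days. A later setback does not change it.
- Employment status is a snapshot. Working at T1 and not at T2 can be seen, but a return that began and failed between two questionnaires cannot.
- Work functioning is observed in a subset formed after randomisation.
- In Table 1 the measures closest to these events (FACIT-F fatigue, depression, job insecurity, support from supervisor and colleagues) are marked for survivors at baseline only. Conflict at work has no described follow-up measure in either arm.

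**Step 4. What the indirect route can detect**

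The planned sample size is reproduced first. Inputs from Sample size calculation: SD 13 h, difference 5.5 h, power 80%, alpha 0.05 (two-sided, per Statistical analyses).

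n per arm = 2 × (1.960 + 0.842)² × 13² / 5.5² = 87.7, rounded up to 88, as stated. Then 176 / 0.75 = 234.7, or 235, against 236 stated.

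With 88 per arm, the difference detectable with 80% power on a 0 to 100 scale is (1.960 + 0.842) × SD × √(2/88) = 0.422 × SD. The documents give no SD for QLQ-C30. For an assumed SD of 15 to 25 points, this is 6.3 to 10.6 points. A randomised comparison of average deterioration is therefore feasible at 12 months.

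**Step 5. What a both-arm event item could detect**

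With 88 per arm and an assumed control-arm frequency of 5% or 10%, 80% power needs about 18.6% or 26.2% in the STEPS arm. New items would therefore serve for estimation with an interval, not as a sensitive test.

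**The case against.** The strongest reply is that harm is already compared. Both arms report sick leave, employment status, work ability, quality of life and health care use to month 12, and the outcome analysis gives the T2 effect separately. This stands. A reader might infer from Table 3 that harms cannot be compared between arms at all, that everything after month 6 is lost, or that half of the randomised participants contribute no harms data. The documents support none of these, because the measures in step 2 cover both arms and both follow-up times.

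Second, the item asks about effects of the programme, which controls cannot answer. This also stands. It is why the item should not simply be copied to the control arm, and why the STEPS count should not be read as a background rate of setbacks. Nor is the direction of any bias known: unblinded participants may over- or under-attribute.

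Third, the word only is an inference. The Table 3 entry names no questionnaire version, so the providers' questionnaire may be a second source, and the full protocol may hold further adverse-event reporting. This stands in part. However, the providers deliver STEPS and are surveyed at the end of the intervention period, so that source would add neither a comparator nor a 12-month round. The point rests on the collection rule the article states, not on detail it leaves out.

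Fourth, the low-risk sentence only justifies having no interim analysis, and an end-of-study tabulation would not change that. This is correct, and the point does not rest on that sentence.

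**Conclusion.** The concern holds in a limited form. As described, explicit adverse effects are collected in one of four arm-by-time cells, so they cannot be compared between arms or followed to 12 months. Harm is visible only indirectly, through outcomes measured in both arms. Those allow a randomised comparison of average worsening but do not identify events such as conflict at work or a failed return.

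The primary estimate, its analysis and the sample size are unaffected. The loss is in how the trial can report on harm.

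The conclusion assumes that the Table 3 item is put to survivors, or at most also to the providers, and that no other adverse-effect collection exists in documents not shown. It also takes Table 1 as complete for the additional variables. That is not certain, since Table 2 says cancer recurrence is asked at follow-up while Table 1 marks it for survivors at baseline only.

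**What to change.** - Add a few neutrally worded yes/no items, limited to what existing measures do not capture, to the T1 and T2 questionnaires of both arms. Examples, each for the past 6 months: a return to work that failed or was reversed, conflict at work, health worsened by working.
- Tabulate them by arm and time point with a risk difference and 95% confidence interval, as estimates rather than tests.
- Keep the programme-attribution item in the STEPS arm only, and name the questionnaire version in Table 3.
- Report the existing both-arm outcomes (sick-leave days, employment status, work ability, QLQ-C30, EQ-5D-5L, health care use) alongside as indirect evidence on harm.

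The cost is a slight extra questionnaire burden and a minor amendment, with no new contacts because the questionnaires already go out. The answers remain unblinded self-reports, so a between-arm difference could still partly reflect reporting.

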### Economic evaluation RCT

An economic evaluation will be conducted using the societal perspective, alongside the RCT, to assess the cost-effectiveness and cost-utility of the STEPS intervention compared to usual care. The costs will be evaluated with: 1) medical consumption costs (direct health care and direct non-health care costs, e.g. taxi costs obtained from the study declarations), 2) costs related to productivity loss (indirect costs) for both the intervention and the control group, and 3) the costs to deliver the intervention program. The effectiveness will be evaluated with: 1) working hours as measured in the trial (primary outcome), and 2) the utility expressed in quality of adjusted life years (QALYs) [54].

Medical consumption costs will be measured using (a selection of questions from) the iMTA’s medical consumption questionnaire for costs outside the hospital (iMCQ) (e.g., home care, informal help) [55]. Standard costs for the Netherlands [54] and prices of prescribed drugs of the Royal Dutch Society for Pharmacy [56] will be used. Costs related to productivity loss will be measured with (a selection of questions from) the iMTA’s productivity costs questionnaire (iPCQ) [55, 57]. To calculate lost productivity due to sick leave, the net number of days on sick leave will be multiplied by the estimated price of production loss of a worker per day of sick leave, based on age and gender. In case of partial sick leave, it will be assumed that cancer survivors were 100% productive during the hours of partial work resumption. The cumulative net number of days of sick leave will be converted into working hour equivalents based on a Dutch average of 1540 working hours per year, according to the Dutch guidelines [54]. To calculate these costs, the friction cost method will be used, which captures lost productivity costs only until an employee would likely be replaced by someone currently unemployed [58]. Both iMCQ and iPCQ questions will be added to the baseline (T0) and follow-up (T1 and T2) questionnaires.

Costs to deliver the intervention will be determined by combining the training costs of the involved occupational therapists and reintegration consultants and the costs to deliver the intervention. Training costs consist of trainer costs (i.e., the expert in the preferred technique), study material costs, and attendance costs for the professionals. Costs to deliver the intervention consist of the mean hours of investment multiplied by the average wage of occupational therapists/reintegration consultant and subsequently multiplied by overhead costs. Also printing costs for the study materials will be considered. All these costs will be calculated according to the Activity Based Costing method [59], in combination with Dutch reference prices [54].

QALYs will be measured based on the utilities from the EuroQol-5D-5L [44], which will be added to the baseline and follow-up questionnaires. The Dutch tariff will be used to estimate the utility of health states described by cancer survivors. QALYs will be calculated by multiplying the utility with the amount of time a cancer survivor spend in a particular health state.

For both cost-utility (expressed in cost/QALY) and cost-effectiveness (expressed in cost/additional working hour) analyses, incremental cost-effectiveness ratios will be calculated by dividing the incremental costs by the incremental effects. The incremental cost-utility ratio indicates the additional costs needed to gain one extra QALY; the incremental cost-effectiveness ratio indicates the additional costs needed for the intervention to gain one extra unit of effect (in our case the primary outcome: additional working hour) compared to usual care. Uncertainty surrounding the input parameters will be estimated using non-parametric bootstrapping with 5000 replications [60]. The 95% confidence intervals around the mean differences will be estimated using the approximate bootstrap confidence algorithm [61]. Bootstrapped cost-effect pairs will be plotted on a cost-effectiveness plane, and a cost-effectiveness acceptability curve will be estimated applying the willingness to pay threshold [62]. The robustness of the model will be tested using various (one-way and two-way) sensitivity analyses.

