	Readiness for return to work	The translated and adapted Dutch version [25] of the original RRTW questionnaire [15]. There are a number of items for each of the phases, with each item being scored on a 1 to 5 scale. Each RRTW stage will be scored by averaging all items within that stage. The stage with the highest summary score was considered the stage the participant was in. In case of a tie between stages, the lowest RRTW stage will be adopted. Based on this participants will be classified in any of the six RRTW phases.	21	6 stages	Ordinal
	Work ability	Single question of the Work Ability Index (WAI) [27], asking participants to estimate their current work ability compared with their lifetime best on 0 to 10 scale (0 = cannot work at all; 10 = best ever);	1	10-point scale	Continuous
Health outcomes	Health-related work functioning	The validated [28] 27-item Work Role Functioning Questionnaire (WRFQ) [29], distinguishing five different work domains: work scheduling demands, mental demands, social demands, physical demands, and output demands (range 0 to 100). Higher scores indicate better work functioning.	27	0 to 100	Continuous
	Health-related quality of life	For patients: the European Organization for Research and Treatment of Cancer Quality of Life Questionnaire – Core 30 (EORTC QLQ C-30) [30]). This 30-item list consists of five multi-item functional scales (i.e., physical, role, emotional, cognitive, and social), three multi-item symptom scales (i.e., fatigue, pain, and nausea and vomiting), six single-item (i.e., dyspnoea, insomnia, appetite loss, constipation, diarrhoea, and financial impact), and a two-item global health and quality of life scale, all with a scoring range from 0 to 100. A higher score on the functional and global health and quality of life scales indicates better quality of life, while on the symptom scales, a higher score indicates a higher level of symptom burden. A summary score will be generated, calculated as the mean of all combined scale scores, excluding financial impact and the global health and quality of life scale.	30	0 to 100	Continuous
		For partners: 12-item short-form health survey (SF-12) [31], expressed in t-score.	12	n/a	Continuous
	Caregiver burden	The ‘Ervaren Druk door Informele Zorg-plus’ (EDIZ) [32], consisting of 15 items, ranging from 0 to 1, higher scores indicate a higher caregiver burden	15	0 to 15	Continuous

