## Discussion

In this paper, the rationale for the STEPS study has been described consisting of: 1) a multi-centre RCT to assess the (cost-)effectiveness of the STEPS intervention, a multidisciplinary, Stages of Change-based intervention combining occupational therapy and reintegration consultation to support RTW and work retention in cancer survivors, and 2) a prospective cohort study to assess work- and health-related outcomes in partners of cancer survivors and to study which factors predict these outcomes. Regarding the RCT, it is hypothesised that the STEPS intervention, compared to usual care, will be cost-effective and effective regarding the primary and secondary health and work-related outcome measures. The extra costs of the STEPS program likely outweigh against the gains in reduced productivity loss. If proven to be (cost-)effective, the STEPS intervention will be a valuable addition to standard care for cancer survivors, which currently varies greatly in the extent to which work-related issues are addressed [4]. Results from this RCT will also help to improve the work-related care of cancer survivors as it will provide insights into which elements of work-related care are effective and which elements are not. Regarding the cohort study, it is hypothesised that living with a cancer survivor will have a substantial negative impact on work- and health-related outcomes of the partners of these survivors. Moreover, factors that that predict the development of these outcomes are expected to be identified. This information can be used to better tailor support for cancer survivors’ partners.

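### Counting hours of partial work resumption as fully productive sets loss at work to zero in that group and can bias incremental productivity cost in either direction

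*Protocol article*

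**What the plan says.** All of the costing rules are in the protocol article, Economic evaluation RCT.

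- **Perspective:** "An economic evaluation will be conducted using the societal perspective, alongside the RCT". One of its three cost categories is "costs related to productivity loss (indirect costs) for both the intervention and the control group".
- **Instrument:** productivity loss is measured with the iPCQ, or some of its questions, at T0, T1 and T2. The article does not say which questions.
- **Calculation:** the only one given is for loss due to sick leave, namely net sick-leave days times a price per day by age and gender. It is valued by friction costs: "the friction cost method will be used, which captures lost productivity costs only until an employee would likely be replaced".
- **Partial sick leave:** "it will be assumed that cancer survivors were 100% productive during the hours of partial work resumption".
- **Sensitivity analyses:** one-way and two-way analyses are promised, but none is named.

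Elsewhere, Tables 1 and 2 list the Work Role Functioning Questionnaire (WRFQ, 0 to 100; "Higher scores indicate better work functioning") and a 0 to 10 work ability item as secondary outcomes at T0, T1 and T2. The WRFQ is completed by those who have partly or fully returned to work, which includes the group that the 100% assumption covers. The Discussion says: "The extra costs of the STEPS program likely outweigh against the gains in reduced productivity loss".

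**The concern.** The 100% assumption is a fixed rule, not a detail lost in condensing a longer document. It fits badly with the rest of the trial. The Background describes fatigue, pain and cognitive difficulties that may affect working life. Entry requires chemotherapy and/or radiotherapy, partly because such survivors report lower work ability than those treated by surgery alone. The Measurements section explains that return to work in the Dutch system is usually a gradual build-up of hours, so partial resumption is the usual route.

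A rule that cannot register output per hour will value an hour at reduced capacity the same as a full one. Incremental cost is the numerator of both the cost per QALY and the cost per additional working hour, and it feeds the acceptability curve. The Discussion's economic argument also rests on savings in productivity. An error in this term therefore goes straight into the cost-effectiveness conclusion. The effectiveness analysis of working hours is not affected.

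**Working it through.** **The plan's own figures.** The article gives no figure for productivity cost or savings. The only number that bears on the point is the expected effect of 5.5 hours per week (SD 13, 80% power, two-sided 0.05; Sample size calculation and Statistical analyses). It reproduces the stated sample size: n = 2 × (1.960 + 0.842)² × 13² / 5.5² ≈ 87.7, so 88 per group and 176 in total. Then 88 / 0.75 = 117.3, so 118 per arm and 236 in total.

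**Set-up.** Let d = 5.5 be the extra hours per week under STEPS. Let H be mean weekly hours at work in the control arm, and p_C and p_I the output per hour at work, as a fraction of full output, in the control and STEPS arms. H, p_C and p_I are not in the documents; they are assumptions shown over a range. As a simplification, the whole difference in hours is treated as avoided absence that is valued, and the friction cap is ignored.

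- Gain credited under the 100% rule: d
- True gain in output: (H + d) × p_I − H × p_C

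**Case 1: equal productivity p in both arms.** The true gain reduces to d × p, and credited over true is 1/p.

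| p (assumed) | True gain, h/week | Credited but not produced, h/week | Credited / true |
|---|---|---|---|
| 0.9 | 4.95 | 0.55 | 1.11 |
| 0.8 | 4.40 | 1.10 | 1.25 |
| 0.7 | 3.85 | 1.65 | 1.43 |
| 0.6 | 3.30 | 2.20 | 1.67 |

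If p_I is below p_C, the overstatement is larger. With H = 15, p_C = 0.8 and p_I = 0.75, the true gain is 20.5 × 0.75 − 15 × 0.8 = 3.38 h/week.

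**Case 2: STEPS raises productivity at work.** The credited and true gains are equal when p_I = (d + H × p_C) / (H + d), which is a rise of d × (1 − p_C) / (H + d) over p_C.

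- With H = 15 and p_C = 0.8: p_I = 17.5 / 20.5 = 0.854, a rise of 5.4 points.
- At p_I = 0.90: true gain = 20.5 × 0.90 − 12 = 6.45 h/week. The rule credits 5.5 and so understates the benefit.
- With p_C = 0.8 and H = 5, 10, 15, 20 or 25, the break-even rise is 10.5, 7.1, 5.4, 4.3 or 3.6 points.
- Over H = 5 to 25 and p_C = 0.6 to 0.9, it runs from 1.8 to 21 points.

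The sign of the bias thus depends on quantities that the rule leaves out.

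**The case against.** **The savings for STEPS need not be overstated.** A reader might infer that full credit for extra hours must favour the arm that gains hours. The documents do not support that. STEPS includes energy management and self-efficacy training (STEPS intervention), and the Discussion hypothesises benefit on the secondary outcomes, which include work functioning and work ability. If that benefit is large enough, the rule hides it (case 2). This objection stands: the direction is open.

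**Loss at work may be costed elsewhere.** A reader might also infer that the plan counts absence only. The sick-leave calculation and the 100% assumption are each confined to sick leave, the cost category is broader, and the selected iPCQ questions are not given, as is normal in a condensed article. It is fair to say only that no other costing is described. If the selected questions do cover loss at work, however, they conflict with the 100% assumption for partial resumption, and the two need reconciling.

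**The amount is uncertain.** One could multiply 5.5 hours by 26 or 52 weeks and speak of 143 to 286 credited hours. That is an upper bound. Absence beyond the friction period carries no cost, the 5.5 hours apply to a sample that includes people already fully at work, and a full year assumes that the effect persists. This objection stands too.

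**The proxies are imperfect.** The WRFQ is a functioning score, and the work ability item compares with lifetime best, not with normal output. Nothing in the documents supports either as a direct multiplier in the base case. That is a reason to keep them to sensitivity analysis.

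**Sensitivity analyses are already promised.** None is named, so none is bound to test this assumption. The bootstrap covers sampling uncertainty, not a constant fixed at 100%.

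**Conclusion.** The point holds as a risk of bias in either direction in the economic evaluation. For hours of partial resumption, loss at work is set to zero by a stated rule, while the evaluation claims a societal perspective and the trial collects related data in the same people.

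If STEPS adds hours at equal or lower at-work productivity that is below 100%, savings are overstated. At equal productivity of 0.9 to 0.7, the factor is 1.11 to 1.43 for the hours that are valued at all. If STEPS raises at-work productivity beyond the break-even (5.4 points at 15 control hours and control productivity of 0.8), savings are understated. The productivity levels and control hours are assumptions, and only the 5.5 hours comes from the protocol. The documents fix neither the direction nor the sum in money.

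**What to change.** State which iPCQ questions are used.

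- **If they cover loss at work:** use them to value hours of partial resumption in place of the 100% assumption.
- **If they do not:** keep 100% as the base case and prespecify one named sensitivity analysis, reported beside it, that relaxes productivity separately in each arm over a stated range (for example 0.6 to 1). The observed WRFQ or work ability at T0, T1 and T2 should inform which part of the range is plausible. A grid over the two arms fits the two-way analyses already promised. Both ratios and the acceptability curve should be shown under it.

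Settle this before the data are analysed, because the Randomization section says that the analysts are not blinded.

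The cost is a little extra analysis and no new data collection. The drawback is that the WRFQ and work ability are only proxies for productivity, so the result shows how far the conclusion depends on the assumption and does not give a corrected cost.
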